### Sample size calculation

As linear mixed models will be used for conducting the primary analyses, it is recommended to base the sample size calculation on a multivariate model [79]. Power analyses for MANOVA were conducted with G*power 3.1.9.2. We want to be able to demonstrate an effect size of 0.25 (partial eta squared) on the primary outcome, while setting the alpha = 0.05 (two tailed) and power = 0.80. With two groups and three measurements each, a sample size of 152 is needed. Taking into account a dropout rate of approximately 20%, a sample size of 190 (95 patients per condition) will be included at baseline.

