## Background

Depressive symptoms, fear of cancer recurrence, and cancer-related fatigue are prevalent symptoms among cancer survivors. It is estimated that 22–87% of cancer survivors report moderate to severe fear of cancer recurrence and 8–21% of cancer survivors meet criteria of depression, based on diagnostic interviews or exceeding a cut-off of clinically significant symptoms on self-report measurements [1, 2]. Severe fatigue is also highly prevalent during and after cancer treatment, in at least a quarter of cancer survivors [3, 4]. Presence of fatigue, depression, and/or fear of cancer recurrence is associated with impaired quality of life and daily functioning. In addition, depressive symptoms, fear of cancer recurrence, and fatigue often co-occur and can exacerbate each other [1–3, 5, 6].

Previous studies evaluated interventions for fear of cancer recurrence, depression, and fatigue in cancer survivors or patients with cancer [7–12]. The vast majority of these interventions are based on a cognitive behavioral model which assumes that although cancer and cancer treatment may trigger the psychological symptoms and fatigue, cognitive and behavioral factors subsequently perpetuate the symptoms [7, 8, 11]. Interventions targeting these perpetuating factors have been shown to decrease symptoms and improve functioning. However, effect sizes are mostly small and sometimes of a moderate magnitude, especially for the treatments aimed at fear of cancer recurrence and depressive symptoms [7, 10, 12]. Also, treatment effects are not always sustained at long-term follow-up [8] and attrition rates are relatively high [13].

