### Study design

This randomized controlled trial is designed as a non-blinded, parallel group, two-arm superiority trial with a 1:1 allocation ratio. The two treatment arms are (a) personalized cognitive behavioral therapy and (b) standard cognitive behavioral therapy. Patients in the standard treatment arm receive an evidence-based protocolized CBT for depressive symptoms, fear of cancer recurrence, or cancer-related fatigue. Patients in the personalized treatment arm also receive CBT for depressive symptoms, fear of cancer recurrence, or cancer-related fatigue. However, the treatment in the personalized treatment arm is systematically tailored to the individual. Tailoring takes place on four dimensions: (1) the allocation of treatment modules, (2) treatment delivery (face-to-face, internet-based or blended), (3) patients’ needs regarding the symptom for which they want to receive treatment, and (4) treatment duration. Primary outcome (limitations in daily functioning) and secondary outcomes (symptom level and quality of life) are evaluated at baseline (T0) and 6 months (T1) and 12 months (T2) after intake. At the end of treatment, goal attainment is evaluated and therapist time is assessed. Drop-out rates are measured during the study. The overall study design is illustrated in Fig. 1. The study protocol has been approved by the Medical Ethics Committee of Amsterdam UMC, University of Amsterdam, Amsterdam, the Netherlands (reference no. 2018_277). The study is registered in the Dutch Trial Registry (NTR): NL7481 (NTR7723).

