### Statistical analyses

#### Primary and secondary study parameter(s)

Descriptive statistics will be used to describe baseline characteristics of the experimental and control group and a chi-square test or independent *t*-test will be used to compare baseline characteristics of dropouts and completers in the total sample. Intention to treat analyses will be conducted, i.e., all randomized patients are included and are analyzed in their randomly assigned treatment group. For the intention to treat analyses, linear mixed-model analyses will be performed to evaluate changes in patient functioning from baseline to 6 and 12 months of follow-up (T1 and T2) and differences therein between the experimental group and the control group. Condition, time, and a group × time interaction will be added to the model (as fixed effects) to test for differences between the groups in treatment effects over time. In addition, a random intercept will be used to allow individuals to differ in the level of their outcome variables. Treatment center and manner of referral (self-referral versus referral by treating doctor) will be used as covariates. Based on pooled pre-test standard deviations, effect sizes will be calculated for the estimated differences between T0, T1, and T2 between groups. A significance level of *p*<0.05 is used in all analyses. Since linear mixed model analysis can handle missing observations due to dropout (assuming data are missing at random), imputation of missing values will not be needed. However, patterns of missing data will be explored and predictors of missing data analyzed, especially if these vary by treatment arm. If the primary analysis shows significant effects of personalized CBT, additional sensitivity analyses will be conducted using different assumptions about the value of missing values. Statistical analyses will be performed using SPSS 24.0. The statistical procedure as described above will also be followed for secondary study parameters (fatigue, depressive symptoms, fear of cancer recurrence and quality of life) without the sensitivity analyses. The independent *t*-test will be used to analyze differences between both groups with respect to goal attainment and therapist time.

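### The stated target effect (partial eta squared 0.25) and the stated sample size (152) are incompatible: 152 patients correspond to a partial eta squared of about 0.06

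*Protocol article*

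**What the plan says.** All the figures are in the protocol article, section Sample size calculation.

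- Method: "Power analyses for MANOVA were conducted with G*power 3.1.9.2". The particular MANOVA option and any within-patient correlation are not given.
- Target: "We want to be able to demonstrate an effect size of 0.25 (partial eta squared) on the primary outcome".
- Error rates: "while setting the alpha = 0.05 (two tailed) and power = 0.80".
- Result: "With two groups and three measurements each, a sample size of 152 is needed".
- Enrolment: "Taking into account a dropout rate of approximately 20%, a sample size of 190 (95 patients per condition) will be included at baseline".

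Study design describes a "two-arm superiority trial with a 1:1 allocation ratio". Under Statistical analyses, the primary mixed model includes a group-by-time interaction "to test for differences between the groups in treatment effects over time". The target is not expressed in SIP-8 points or as a standardised mean difference, so the partial eta squared is the article's only statement of what the trial can detect on its primary outcome.

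**The concern.** Partial eta squared 0.25 means that the tested effect accounts for a quarter of the variance left to that effect and its error. That is a very large difference to expect between two active CBT arms, and so large an effect should need far fewer than 152 patients. Meanwhile 0.25 is a familiar value on a different scale, Cohen's f, where it corresponds to partial eta squared of about 0.06. This suggests that the number and its label come from different scales.

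What is at stake is how the result is read. The Discussion says that, if the arms do not differ, expectations of personalised treatment may need rethinking. How far a null result supports that depends on the effect the trial could have detected. The same section reports that earlier head-to-head comparisons in non-cancer populations mostly found no significant difference, which makes a target of this size harder to credit. Background adds that for existing interventions "effect sizes are mostly small and sometimes of a moderate magnitude". That is weaker support, because it concerns the interventions' own effects and not the difference between personalised and standard CBT.

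**Working it through.** **Inputs (Sample size calculation, Study design).** Effect 0.25 labelled partial eta squared; two-sided alpha 0.05; power 0.80; two groups, 1:1; three measurements; N = 152; dropout 20%.

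**Assumed test.** Repeated-measures MANOVA, within-between interaction. It fits two groups with three measurements and the group-by-time term of the primary model. The statistic is noncentral F with df1 = 2, df2 = N − 3 and noncentrality λ = N × f², where f² = η²p / (1 − η²p).

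**Step 1: the dropout step.** 152 / (1 − 0.20) = 190. This reproduces.

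**Step 2: N from the stated inputs.** f² = 0.25 / 0.75 = 0.333, so f = 0.577.
- N = 33: λ = 11.0, power 0.813. N = 32: power 0.799. The requirement is therefore 33, or 34 with equal arms.
- N = 152: λ = 50.7, power above 0.9999.

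The stated 152 is not reproduced.

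**Step 3: does another test give 152 at partial eta squared 0.25?**
- Numerator df of 1, 2 or 3: 26, 33, 37.
- The same tests with smaller noncentrality conventions: at most 41.
- Between-factors test, correlation 0 to 0.9: 11 to 25.
- Correlation-based within-between tests: 6 to 14.

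The range is 6 to 41. Reading 0.25 as f² gives 42 for the 2-df test and at most 52 across variants. None approaches 152.

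**Step 4: what 152 patients can detect.** Solving for 80% power at N = 152:

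| Test | f² | f | η²p | 0.25 / η²p | 0.577 / f |
|---|---|---|---|---|---|
| 1 df | 0.0523 | 0.229 | 0.050 | 5.0 | 2.5 |
| 2 df (within-between) | 0.0647 | 0.254 | 0.061 | 4.1 | 2.3 |
| 3 df (three-response) | 0.0736 | 0.271 | 0.069 | 3.6 | 2.1 |

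**Step 5: is 0.25 a Cohen's f?** f² = 0.0625, so η²p = 0.0625 / 1.0625 = 0.059.
- 2-df test: N = 158 (power 0.802). At N = 152, λ = 9.5 and power is 0.785.
- 1-df test: N = 128, power at 152 of 0.86. 3-df test: N = 179, power at 152 of 0.72.
- Between-factors test at correlation 0.5: N = 86.
- Partial eta squared entered as 0.06, 2-df test: N = 154.

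Reading 0.25 as f comes close to 152 but does not return it exactly.

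**Step 6: scale as a standardised difference.** Assume equal effects d at T1 and T2 and a common correlation r between measurements. Then λ = (N/4) × d² × 2 / [3(1 − r)], which gives d = f × √[6(1 − r)].

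| r (assumed) | d at f = 0.25 | d at η²p = 0.25 |
|---|---|---|
| 0.3 | 0.51 | 1.18 |
| 0.5 | 0.43 | 1.00 |
| 0.7 | 0.34 | 0.77 |

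**The case against.** The core mismatch has no good defence: nothing else in the article corrects the label, and no test tried rescues it. The objections concern how far the point goes.

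- **The test is not named.** The sample size of 158 and the power of 0.785 hold only for the within-between MANOVA. The G\*Power settings may be in the full protocol, and their absence from an article is not a fault. This stands. It limits what can be said about the intended input, but not the contradiction between the printed effect and the printed N.
- **The intended entry is not proven.** A reader might infer that f = 0.25 was certainly entered and that N should have been 158. The documents do not support that: f = 0.25 gives 128, 158 or 179 depending on the test, and partial eta squared 0.06 comes closer to 152 than f = 0.25 does under the 2-df test. A mislabelled f remains the likeliest explanation only.
- **The size depends on the scale.** The gap is about four-fold in partial eta squared but about 2.3-fold in f. Both should be given.
- **Little changes in practice.** The primary analysis is an intention-to-treat mixed model that also uses partial data, so power at 152 complete cases is not the trial's exact power. Observed effect sizes, scaled by pooled pre-test standard deviations, will be reported in any case. This stands too: no analysis or recruitment decision turns on the error. It is still a wrong figure for the central design assumption.

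**Conclusion.** The point holds. As printed, partial eta squared 0.25 and N = 152 cannot both be right. The stated effect needs about 34 patients, at most 41 under any variant tried. At 152 patients, the effect detectable with 80% power is partial eta squared of about 0.061 (f about 0.254) under the assumed within-between MANOVA, and about 0.05 to 0.07 across 1- to 3-df tests. The stated detectable effect is therefore about 3.6 to 5 times too large in partial eta squared, and about 2.3 times (2.1 to 2.5) in f.

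The mismatch itself does not depend on which test was used. The value near 0.061 does, and the d figures also rest on assumed correlations and equal effects at T1 and T2.

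A reader might infer that the trial is underpowered. The documents do not show that: 152 is far more than the stated effect would need, and the step to 190 is correct. What is wrong is the statement of what the trial can detect.

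**What to change.** In Sample size calculation:

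1. Check the saved G\*Power output, then name the test and the inputs actually used.
2. Replace the effect label with the value that corresponds to 152: partial eta squared of about 0.06, f about 0.25, adjusted to whatever the output shows.
3. If f = 0.25 in the within-between interaction MANOVA was intended, restate power at 152 complete cases as about 0.785.

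The recruitment target of 190 can stay. The cost is a change of wording, with no additional patients and no change to the analysis. The article reports recruitment as ongoing, so the correction should be made and dated before results are known.

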## Discussion

To our knowledge, this is the first study comparing the efficacy of personalized CBT to standard CBT in cancer survivors with moderate to severe fear of cancer recurrence, depressive symptoms, and/or cancer-related fatigue. The study has several innovative characteristics.

The first is the head-to-head comparison between personalized CBT and standard CBT. There has been a repeated call for personalized psychological treatments for cancer patients [15–17]. Multiple studies have applied personalization in cognitive behavioral therapy (CBT) for cancer survivors or patients with cancer [18–28]. However, to the best of our knowledge, only one study compared personalized CBT to standard CBT [19]. In the other studies, personalized CBT was compared to a wait list group or another intervention such as a psycho-education. To determine if and the extent to which personalized CBT has added value over standard CBT in cancer survivors, more studies with a head-to-head comparison are needed. Our study enables a direct comparison.

A second innovative characteristic of this study is the personalization of psychological treatment on various dimensions. Other studies, in which the efficacy of personalized CBT was compared to standard CBT in non-cancer patients, mostly found no significant difference between the two treatment forms. Researchers suggested that insufficient contrast between the two interventions could have partly accounted for the lack of difference [80–82]. Therefore, we aimed to expand the contrast in this study by delivering a package of personalization measures. Should these measures eventually not lead to a difference between treatment arms, the expectations of the added value of personalized psychological treatments should perhaps be reconsidered. However, if personalized CBT appears to be more efficacious than standard CBT, it will remain unclear which personalization measure or combination of personalization measures explains the difference. Further research could then explore the extent to which each personalization measure adds value to personalized CBT. For example, the MOST design could be used to further optimize the intervention [83]. For clarity, we decided to personalize CBT on multiple dimensions to maximize the contrast between personalized CBT and standard CBT.

Another innovative characteristic of this study is the application of EMA in clinical practice, specifically for systematically personalizing CBT. Nowadays, electronic sampling devices provide the opportunity for rapid analysis and availability of real-life experimental data. Recent studies suggested not to use EMA merely as an instrument to monitor, but as a tool to provide feedback and treatment recommendations [32, 63, 84]. In this study, we further concretize how EMA can be used for personalizing psychological treatment in clinical practice, by presenting care providers with prospective information on patients’ psychological symptom patterns, behavior, and contextual influences in daily life, with minimal delay. Individual symptom patterns over time will be identified and thereby the factors that maintain symptoms in specific individuals. The use in clinical practice is promising and a logical next step, but is also new and innovation comes with vulnerabilities. In some patients, symptoms may fluctuate too little, as a result of which no valid EMA models can be formed. For this study, we solved this potential problem by having questionnaires as a back-up. However, as mentioned before, the presence of a maintaining factor identified with a questionnaire does not automatically imply that the factor influences symptom level. Therefore, EMA seems the most desirable approach to determine the maintaining factors, which subsequently inform the direction for treatment.

Previous studies showed that there are large individual differences in how quickly patients respond to interventions [39, 40]. In this study, we aimed to adjust treatment duration on the individual level by adding an “in-between” assessment and evaluating the extent to which treatment goals already have been reached after completing several treatment modules. If treatment continues, the second EMA determines which treatment modules to add or repeat. A previous study in which personalized CBT was compared to standard CBT in a non-cancer population found a beneficial effect of personalized CBT and suggested that this beneficial effect was found because the therapeutic sessions were longer [85]. The current study will provide additional information on the needed treatment duration in personalized CBT compared to standard CBT, and on the extent to which treatment duration differs within the personalized CBT group. Although we will not conduct cost effectiveness analyses, we will have an indication of the costs by therapist time and number of treatment sessions.

In conclusion, this study meets the repeated call for personalized psychological treatment, and the movement towards patient-centered care. This study is an important step, as it will provide much needed evidence regarding if personalized CBT is more efficacious than standard CBT. One could argue that therapists already aim to deliver personalized treatments in clinical practice. However, the challenge is to develop an evidence-based framework for personalizing CBT in a systematic and replicable way [86]. The explicitly operationalized personalization dimensions in this study have the potential to provide the first step in developing this kind of framework.

## Trial status

Protocol version 4.0, 22 January 2021. Recruitment is ongoing.

Recruitment of participants for this study started in February 2019 and is scheduled to finish in June 2022.

## Data Availability

The dataset belonging to this study is not available yet.
